## Abstract

**Background:**

Stroke produces multiple symptoms, including sensory, motor, cognitive and psychological dysfunctions, among which motor deficit is the most common and is widely recognized as a major contributor to long-term functional disability. Robot-assisted training is effective in promoting upper extremity muscle strength and motor impairment recovery after stroke. Additionally, action observation treatment can enhance the effects of physical and occupational therapy by increasing neural activation. The AOT-EXO trial aims to investigate whether action observation treatment coupled with robot-assisted training could enhance motor circuit activation and improve upper extremity motor outcomes.

**Methods:**

The AOT-EXO trial is a multicentre, prospective, three-group randomized controlled trial (RCT). We will screen and enrol 132 eligible patients in the trial implemented in the Department of Rehabilitation Medicine of Tongji Hospital, Optical Valley Branch of Tongji Hospital and Hubei Province Hospital of Integrated Chinese & Western Medicine in Wuhan, China. Prior to study participation, written informed consent will be obtained from eligible patients in accordance with the Declaration of Helsinki. The enrolled stroke patients will be randomized to three groups: the CT group (conventional therapy); EXO group (exoskeleton therapy) and AOT-EXO group (action observation treatment-based exoskeleton therapy). The patients will undergo blinded assessments at baseline, post-intervention (after 4 weeks) and follow-up (after 12 weeks). The primary outcome will be the Fugl-Meyer Assessment for Upper Extremity (FMA-UE). Secondary outcomes will include the Action Research Arm Test (ARAT), modified Barthel Index (MBI), kinematic metrics assessed by inertial measurement unit (IMU), resting motor threshold (rMT), motor evoked potentials (MEP), functional magnetic resonance imaging (fMRI) and safety outcomes.

**Discussion:**

This trial will provide evidence regarding the feasibility and efficacy of the action observation treatment-based exoskeleton (AOT-EXO) for post-stroke upper extremity rehabilitation and elucidate the potential underlying kinematic and neurological mechanisms.

**Trial registration:**

Chinese Clinical Trial Registry ChiCTR1900026656. Registered on 17 October 2019.

**Supplementary Information:**

The online version contains supplementary material available at 10.1186/s13063-021-05176-x.

## Background

Stroke is the leading cause of mortality and disability worldwide, placing a significant burden on healthcare facilities and socioeconomic systems [1]. Stroke produces numerous symptoms, including sensory, motor, cognitive and psychological dysfunctions, among which motor deficit is the most common and is widely recognized as a major contributor to long-term functional disability [2, 3]. Upper-extremity motor impairments manifest in loss of fractionated movement, coordination and dexterity, resulting in limitations in activities of daily living (ADL) and social participation [4]. Over the last several decades, various rehabilitation approaches have been developed to promote upper extremity motor recovery, functional performance and quality of life in stroke patients [5, 6]. These novel approaches are commonly predicated on the principles of motor learning and task-specific training to facilitate motor neural network plasticity [7–9].

Robot-assisted training is an innovative exercise-based technique that involves the principles of motor learning, such as highly repetitive, intensive and task-specific training with feedback [10]. Studies have shown that robot-assisted training can improve arm muscle strength and upper extremity motor impairment [11]. However, the results in terms of arm motor function and ADL after stroke remain debatable [12, 13]. To strengthen the effects of robot-assisted training on arm function and to explore the involved neural mechanisms, researchers have integrated numerous different techniques into the robotic training routine (e.g. functional electrical stimulation, transcranial direct current stimulation, virtual reality). As a training platform, robotic devices can be programmed simultaneously with other techniques in the adaptive, motivational and quantifiable training methods for boosting neuroplasticity [14].

Action observation therapy (AOT) has been applied as an alternative or complement to another approach to rebuild motor function for stroke rehabilitation and was developed on the neurophysiological basis of the mirror neuron system (MNS) [15, 16]. Action observation therapy consists of action observation followed by action imitation and execution, considering that both processes share the matching cerebral motor network. During AOT, patients are instructed to carefully observe the video sequences, imitate them and then practice those movements and motor tasks. Studies have indicated that action observation would induce neural plasticity by promoting activation of the damaged motor circuits that enhance training effects involved in motor learning after stroke [17–19].

Although there have been extensive articles investigating the application of robotic devices and action observation therapy in upper limb rehabilitation after stroke, they fail to show a superior effect in arm function and ADL compared with conventional therapy. Moreover, according to our knowledge, few studies have examined the combined effects and underlying mechanisms of these two techniques. We hypothesize that action observation treatment coupled with robot-assisted training may enhance motor circuit activation and improve upper extremity motor outcomes. Therefore, in this study, we aim to evaluate the effects of action observation treatment-based exoskeleton (AOT-EXO) treatment for the upper extremity after stroke and to explore the potential kinematic mechanisms assessed by inertial measurement unit (IMU) and neurological mechanisms using functional magnetic resonance imaging (fMRI) and corticospinal excitability metrics.

## Methods

### Study design

This protocol follows the Consolidated Standards of Reporting Trials (CONSORT) Statement on randomized trials of non-pharmacological treatment. The study will be reported according to the SPIRIT (Standard Protocol Items: Recommendations for Interventional Trials) statement (Additional file 1). The Clinical Trials Ethics Committee of Huazhong University of Science and Technology provided ethical approval on 24 October 2018. The trial was registered in the Chinese Clinical Trial Registry, ChiCTR1900026656, on 17 October 2019.

The AOT-EXO trial is a multicentre, prospective, three-group randomized controlled trial (RCT). It will be implemented in the Department of Rehabilitation Medicine of Tongji Hospital, Optical Valley Branch of Tongji Hospital and Hubei Province Hospital of Integrated Chinese & Western Medicine in Wuhan, China. A flowchart overview of the study is presented in Fig. 1. The Standard Protocol Items: Recommendations for Interventional Trials (SPIRIT) for enrolment, interventions and assessments is presented in Fig. 2.

**Fig. 1 Fig1:**
[figure not shown]
Study flow diagram

**Fig. 2 Fig2:**
[figure not shown]
Standard Protocol Items: Recommendations for Interventional Trials (SPIRIT)

Prior to study participation, written informed consent (Additional file 2) will be obtained from eligible patients in accordance with the most recent Declaration of Helsinki. In total, 132 eligible subjects will be randomly allocated into three groups equally: (1) CT group (conventional therapy), (2) EXO group (exoskeleton therapy) and (3) AOT-EXO group (action observation treatment-based exoskeleton therapy). All subjects will receive assessments at baseline, post-intervention (after 4 weeks) and follow-up (after 12 weeks). To avoid assessment bias, an independent evaluator at each centre blinded to the randomization procedure and group allocation will complete all outcome measures.

### Participants

The inclusion criteria are as follows: (1) age 18–80, (2) clinical diagnosis of stroke (cerebral infarction, primary intracerebral haemorrhage, subarachnoid haemorrhage) within 6 months before enrolment, (3) Fugl-Meyer Assessment of the Upper Extremity (FMA-UE) score 8–47, (4) Mini-Mental State Examination (MMSE) score ≥ 22 and compliance with the interventions and (5) provision of written informed consent [20, 21].

The exclusion criteria are as follows: (1) more than one stroke (patients with previous transient ischaemic attack could participate); (2) other current significant impairment of the upper limb, e.g. fixed contracture, shoulder subluxation, or recent fracture; (3) severe visual deficits or unilateral spatial neglect; (4) diagnosis likely to interfere with rehabilitation or outcome assessments, e.g. traumatic brain injury, meningitis and epilepsy; and (5) current participation in another upper limb rehabilitation trial [21, 22]. Of note, patients with contraindications to transcranial magnetic stimulation and functional magnetic resonance imaging (e.g. pacemakers, claustrophobia, implanted metal, implantable electronic devices) will NOT be excluded but will NOT receive corticospinal excitability or fMRI examination.

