### Randomization and blinding

The following information will be collected: demographic information, medical history, medication and rehabilitation details, stroke type, time post stroke onset, complications, comorbidity and baseline outcome measures.

We will randomize all the included patients into the three groups at a ratio of 1:1:1 through a computer-generated random number table centrally generated in Tongji Hospital. An independent statistician will prepare the sequentially numbered, opaque, sealed envelopes before the start of enrolment. No randomization number will be reutilized in any case. Because the training methods differ between groups and according to the features of the robot, it is not feasible to blind the subjects, therapists or physicians participating in the trial. Therefore, an independent evaluator at each centre blinded to the randomization procedure and group allocation will assess all outcome measures (baseline, post-intervention and follow-up measures).

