### Outcomes

All outcomes will be measured at baseline, post-intervention (at 4 weeks) and follow-up (at 12 weeks) with no charge. The primary outcome will be mean change in the Fugl-Meyer Assessment for Upper Extremity (FMA-UE) score. This assessment examines arm movement, coordination and reflexes, and the results are represented as a 3-point ordinal scale score with a maximum of 66 points. The FMA-UE is a reliable and valid scale with which to measure upper limb motor impairment after stroke, with higher scores indicating better motor function [24].

Secondary outcomes will be the mean change in Action Research Arm Test (ARAT) score, modified Barthel Index (MBI), kinematic metrics, resting motor threshold (rMT) and motor evoked potentials (MEP), functional magnetic resonance imaging (fMRI) and safety outcomes.

The Action Research Arm Test (ARAT) evaluates 19 tests of arm motor function, including four subscales: grasp, grip, pinch and gross movement. Each test is given an ordinal score of 0, 1, 2 or 3, with the total score ranging from 0 to 57, with higher values indicating better arm motor status and dexterity [25].

The modified Barthel Index (MBI) is an assessment tool formulated to examine the level of independence in the basic ADL and comprises 10 categories: feeding, personal hygiene, toilet use, bladder control, bowel control, bathing, dressing, chair/bed transfer, ambulation, and stair climbing [26].

We will use kinematic metrics (Inertial Measurement Unit, IMU, Noraxon USA Inc.) to evaluate the movement smoothness (peak speed, time to peak speed, number of movement units and path ratio) and performance (pointing time and pointing accuracy) during the finger-to-nose test. The instrumented kinematic assessment can provide good sensitivity for detecting motor performance that is not captured by the clinical scales [27, 28].

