### Statistical analyses

All statistical analyses will be performed using SPSS software (version 21.0, IBM Corporation, Chicago, IL). To assess the normal distribution of quantitative data, the Shapiro-Wilk test will be employed (*P* > 0.05). Continuous variables will be presented as the mean (SD) for normal distributions and median for non-normal distributions and categorical variables will be presented as frequencies or percentages. Baseline data between groups will be compared using Student’s t-test for continuous variables and the chi-square or Fisher’s exact tests for categorical variables. A *P* value < 0.05 will be considered indicative of statistical significance. All analyses will be carried out based on the intention-to-treat principle, with missing data calculated using multiple imputation. Within-group differences will be assessed using paired t tests for the normally distributed data and Wilcoxon-signed rank test for the non-parametric equivalent test. When comparing the two patient subgroups at each time point, Student’s *t* test (for continuous data) and Fisher’s exact test (for categorical data) will be implemented. When examining the effect of the randomization procedure over time, two-way repeated measures analysis of variance (ANOVA) will be conducted to examine the time-treatment group interaction, with time as the within-group variable and treatment group as the between-group variable.

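### Time since stroke onset is recorded at entry but left out of the stated between-group analyses, which gives up precision on FMA-UE change

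*Protocol article*

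**What the plan says.** All references are to the Protocol article.

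- **Participants:** eligibility requires a "clinical diagnosis of stroke (cerebral infarction, primary intracerebral haemorrhage, subarachnoid haemorrhage) within 6 months before enrolment". There is no minimum time since stroke.
- **Randomization and blinding:** the data collected include "stroke type, time post stroke onset, complications, comorbidity and baseline outcome measures". Patients are allocated "at a ratio of 1:1:1 through a computer-generated random number table centrally generated in Tongji Hospital". No stratification or blocking factor is named.
- **Intervention:** routine treatment continues in every arm alongside the 4-week intervention.
- **Outcomes:** "The primary outcome will be mean change in the Fugl-Meyer Assessment for Upper Extremity (FMA-UE) score", with assessments at baseline, 4 weeks and 12 weeks.
- **Statistical analyses:** "When comparing the two patient subgroups at each time point", Student's t test is used for continuous data. The time-by-treatment interaction is tested by two-way repeated measures ANOVA, "with time as the within-group variable and treatment group as the between-group variable". No covariate is named. Separately, "Baseline data between groups will be compared using Student’s t-test for continuous variables", with nothing said about what follows from a difference.
- **Sample size:** differences of 5 points (AOT-EXO versus CT) and 3 points (AOT-EXO versus EXO), SD 5.0, significance level 1.67%, power 0.8, 40 per group, raised to 44 for 10% loss.

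**The concern.** The outcome is a change score, all arms continue routine care, and entry may fall anywhere from the first days to six months after stroke. If spontaneous recovery slows over that period, two patients with the same baseline FMA-UE but different times since onset have different expected changes whatever their arm. The stated ANOVA does not capture this: its time factor is the assessment visit, not time since stroke. Baseline FMA-UE alone would not capture it either.

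Two things are lost. Variation that a recorded baseline variable could explain stays in the residual, so intervals are wider than they need be. And if the realised arms differ in recovery phase, no stated analysis corrects for it. The contrast that isolates action observation, AOT-EXO versus EXO, is the one planned at only 3 points, so it has the least room for avoidable noise.

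**Working it through.** **1. The plan's own figure.** With SD 5.0, two-sided alpha 0.0167 and power 0.8, n = 2(z_alpha/2 + z_beta)² × SD² / difference². Here (2.394 + 0.842)² = 10.47.

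- 5 points: 2 × 10.47 × 25/25 = 20.9, so 21 per group (23 by the t distribution).
- 3 points: 2 × 10.47 × 25/9 = 58.2, so 59 per group (60 by the t distribution).

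The stated 40 is not reproduced by either contrast; one-sided testing at 3 points gives 49 to 51. At 40 per group, power is 0.98 for 5 points and about 0.60 for 3 points. That is a separate matter, used here only as the starting point.

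**2. Variance explained by time since onset.** The article gives no recovery rate and no distribution of entry times, so these are assumptions. Expected spontaneous 4-week gain is A·exp(−t/τ), with t uniform from week a to week 26, A from 8 to 16 points and τ from 4 to 10 weeks. SD 5.0 is taken as the total SD of change.

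- mean = Aτ(e^(−a/τ) − e^(−26/τ)) / (26 − a)
- mean square = A²τ(e^(−2a/τ) − e^(−52/τ)) / (2(26 − a))
- share of variance = (mean square − mean²) / 25

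| Earliest entry | Low (A 8, τ 4): SD, share | Mid (A 12, τ 6): SD, share | High (A 16, τ 10): SD, share |
|---|---|---|---|
| week 1 | 1.45, 8.5% | 2.57, 26.5% | 3.66, 53.5% |
| week 3 | 0.90, 3% | 1.86, 14% | 2.96, 35% |
| week 4 | 0.71, 2% | 1.58, 10% | 2.65, 28% |

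The range is about 2% to 54% and depends strongly on how many patients enter in the first weeks.

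**3. Chance imbalance.** With 40 per arm, the ordinary 95% sampling error of a pairwise contrast is 1.96 × 5 × √(2/40) = ±2.19 points. The part due to imbalance in onset time is 1.96 × SD × √(2/40). For entry from week 1 this is ±0.64 (low), ±1.13 (mid) and ±1.60 (high); for entry from week 4 it is ±0.31, ±0.69 and ±1.16. These lie inside the ±2.19. In the week-1 mid case, the error left after adjustment is 2.19 × √(1 − 0.265) = ±1.88, and √(1.13² + 1.88²) = 2.19.

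**4. Gain from adjustment, 3-point contrast.** Residual SD = 5√(1 − R²); SE = residual SD × √(2/40); noncentrality = 3/SE; noncentral t on 78 df, critical value 2.446. The degrees of freedom spent on covariates are ignored.

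| R² | Residual SD | SE | Noncentrality | Power | n per group for 80% | SE saved |
|---|---|---|---|---|---|---|
| 0 | 5.00 | 1.118 | 2.68 | 0.595 | 60 | – |
| 0.10 | 4.74 | 1.061 | 2.83 | 0.649 | 54 | 5% |
| 0.20 | 4.47 | 1.000 | 3.00 | 0.709 | 48 | 11% |
| 0.30 | 4.18 | 0.935 | 3.21 | 0.775 | 43 | 16% |

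**5. What the SD of 5.0 covers.** Sample size does not say. If it covers the full 0 to 6 month mix, the table above applies. If it described one recovery phase only, with half the patients early and an assumed early-late gap of 4 points, the total SD would be √(25 + 4) = 5.4 and unadjusted power 0.52. With an 8-point gap, it would be √(25 + 16) = 6.4 and 0.37.

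**The case against.** **The article may simply be condensed.** Covariate lists and stratification factors are often left to a fuller protocol or SAP. For randomization this objection stands. A reader might infer that allocation ignores recovery phase, but a computer-generated table can be stratified or blocked, and silence does not show that it is not. For the analysis it carries less weight: the article names the tests, the model and its factors, and time since onset is not among them.

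**Randomization already protects the comparison.** This is correct. A reader might infer that the wide entry window biases the result. It does not: the contrast is unbiased over randomizations and type I error is controlled. Nor is the imbalance of step 3 an extra harm on top of sampling error; it is one component of the ±2.19 points.

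**The noise may already be budgeted.** Also fair. If 5.0 is the total SD, the sample size already carries the recovery-phase spread and the loss is forgone precision only. A reader might infer that the trial is underpowered because of recovery phase, but nothing in the article shows that 5.0 excludes it.

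**The size is assumed.** It is, and entry in the first weeks drives it. Eligibility also requires MMSE of at least 22 and compliance with the interventions, which may make very early entry uncommon and move the share toward the lower rows of step 2.

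**The variable is not wholly unused.** Time since onset is a baseline variable, so it would enter the between-group baseline comparison. No action is tied to that comparison, so it corrects nothing.

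**Conclusion.** The point holds as one of efficiency, not validity. The plan records a variable likely to predict change in FMA-UE, allows it to vary from 0 to 6 months, and states between-group analyses that do not use it. The cost is wider intervals than necessary and no correction if the realised arms differ in recovery phase.

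The size cannot be read from the article. Under the assumed curves the explained share is roughly 2% to 54% of a variance of 25. If adjustment explains 10% to 30%, power for the 3-point contrast rises from about 0.60 to between 0.65 and 0.77, with no added patients; at 2% the gain would be negligible. For the 5-point contrast, power is already 0.98, so the benefit there is narrower intervals. These figures assume 40 per group, two-sided alpha 0.0167 (the article does not state sidedness) and 5.0 as the SD of change.

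**What to change.** In Statistical analyses, prespecify time since stroke onset at entry (for example, log days) and baseline FMA-UE as covariates for the between-group comparison of FMA-UE change. Either of two forms works:

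- an ANCOVA of change at 4 weeks and at 12 weeks, with treatment group and both covariates; or
- a mixed model over the visits with group, visit, group-by-visit and covariate-by-visit terms.

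The covariate-by-visit terms matter. A covariate entered only as a main effect would not adjust the time-by-group interaction that the plan tests. Treat ARAT and MBI likewise, with their own baseline values.

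The cost is a few lines of text: no new data, visits or patients. Trial status reports 12 of the planned 132 enrolled at submission. The covariates should be fixed before outcomes are compared by group, because adding them later would look data-driven.

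Re-stratifying the remaining allocation is not needed. It would mean replacing envelopes prepared before enrolment and, if permuted blocks were used, would make allocation more predictable to unblinded therapists, while the covariate alone secures most of the benefit.

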### Randomization and blinding

The following information will be collected: demographic information, medical history, medication and rehabilitation details, stroke type, time post stroke onset, complications, comorbidity and baseline outcome measures.

We will randomize all the included patients into the three groups at a ratio of 1:1:1 through a computer-generated random number table centrally generated in Tongji Hospital. An independent statistician will prepare the sequentially numbered, opaque, sealed envelopes before the start of enrolment. No randomization number will be reutilized in any case. Because the training methods differ between groups and according to the features of the robot, it is not feasible to blind the subjects, therapists or physicians participating in the trial. Therefore, an independent evaluator at each centre blinded to the randomization procedure and group allocation will assess all outcome measures (baseline, post-intervention and follow-up measures).

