### Intervention

Stroke patients in all groups will require multidisciplinary medication and rehabilitation; hence, their routine treatment programmes will continue as usual with the additional 4-week intervention. The intervention will be delivered at the same frequency and duration in the three groups: 45 min daily, 5 days/week for 4 weeks. The same therapists and therapy assistants will deliver all the intervention sessions at each centre [12].

Participants in the CT group (conventional therapy) will receive the therapist-mediated arm intervention using conventional therapy techniques, such as muscle strengthening, stretching, arm exercises or gross-motor training, fine-motor training and functional task practice. This therapy matches that in the other groups with respect to schedule and the form and intensity of movements. The programmes in the conventional group will progress to meet the patient’s training goals.

The EXO group (exoskeleton therapy) will receive intensive task-specific training in the three-dimensional workspace of the human arm involving shoulder (flexion/extension, horizontal abduction/adduction, external/internal rotation) and elbow (flexion/extension, pronation/supination) movements (Armule®, Intelbot Intelligent Machine Co., Ltd., Wuhan, China). Each training session consists of exercises in the following order: 5-min passive mode plus 15-min assist-as-needed mode for twice with a 5-min break between intervals. In the passive mode, the exoskeleton manipulates the upper limb in a three-dimensional trajectory predetermined by the therapists according to the patient’s goals. In the assist-as-needed mode, the patients practice games and ADL training programmes dedicated to shoulder and elbow movements. When the patient is unable to complete the tasks actively, assistive force will supply the upper extremity with passive movement to the target positions.

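### Three centres with their own evaluators and therapists, but no centre term in the stated analysis and no stratification by centre named: a loss of precision, not a bias

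*Protocol article*

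**What the plan says.** - **Centres.** Study design names three sites: "Tongji Hospital, Optical Valley Branch of Tongji Hospital and Hubei Province Hospital of Integrated Chinese & Western Medicine in Wuhan, China".
- **Allocation.** Randomization and blinding says that patients are allocated "at a ratio of 1:1:1 through a computer-generated random number table centrally generated in Tongji Hospital". It adds: "An independent statistician will prepare the sequentially numbered, opaque, sealed envelopes before the start of enrolment". It names no stratification factor or blocking, and does not say whether envelopes are issued per centre. Study design says that "132 eligible subjects will be randomly allocated into three groups equally".
- **What is tied to a centre.** For outcomes, "an independent evaluator at each centre blinded to the randomization procedure and group allocation will assess all outcome measures". For treatment, "The same therapists and therapy assistants will deliver all the intervention sessions at each centre".
- **Routine care.** For all patients, "their routine treatment programmes will continue as usual with the additional 4-week intervention". The article does not say whether these programmes differ between centres.
- **Analysis.** The primary outcome is mean change in FMA-UE (Outcomes). Statistical analyses compares groups by Student's t test and by a two-way repeated measures ANOVA, with time within subjects and treatment group between subjects. Centre is not among the factors.
- **Targets.** Sample size assumes 5 points for AOT-EXO versus CT, 3 points for AOT-EXO versus EXO, SD 5.0, a significance level of 1.67% per comparison, and 44 randomised per group.

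**The concern.** Patients at one centre share an evaluator and a therapy team, so mean FMA-UE change could plausibly differ by centre. Such differences can be handled by stratifying the allocation, by putting centre in the model, or by both. The article describes neither.

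Two things are then at stake. Between-centre variation enlarges the error term of every group comparison. And if one arm happens to draw more patients from a centre with larger changes, nothing in the described analysis corrects for it. The 3-point AOT-EXO versus EXO contrast has the least room for either.

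**Working it through.** **Inputs from the article:** 132 patients, 44 per arm, SD 5.0, target 3 points, level 1.67% (taken as two-sided; the article does not say).

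**Assumptions, not in the article:** centre effects on FMA-UE change of -2/0/+2 or -4/0/+4 points; centre shares equal or 60/20/20; SD 5.0 read as the within-centre SD. The closed forms below use equal shares.

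**The plan's own figure.** There is no stated figure for centre effects. The stated 40 per group could not be reproduced: at two-sided 1.67%, 3 points needs 59 per group and 5 points needs 21. That is a separate matter, and nothing below depends on it.

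**1. Imbalance in centre share, unstratified list, 44 per arm.** The SD of the difference between two arms in one centre's share is √(2/9 × 132/131 × 2/44) = 0.101. The 95% bound is 1.96 × 0.101 = 0.20, or 20 percentage points. Simulation gave the same.

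**2. Resulting shift in a pairwise contrast.** The variance of the centre effects is (4+0+4)/3 = 2.67 or (16+0+16)/3 = 10.67.
- ±2: SD = √(2.67 × 132/131 × 2/44) = 0.35; 95% bound 0.68 points, or 23% of 3.
- ±4: SD = 0.70; 95% bound 1.37 points, or 46% of 3.

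Over 6,000 simulated trials per scenario, the mean shift was about zero and the bounds were 0.65–0.70 and 1.36–1.38 points. With allocation stratified by centre they fell to 0.09–0.11 and 0.18–0.22.

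**3. Type I error of the unadjusted t test.**
- Unstratified list: 1.5–2.0% simulated, against a nominal 1.67%. This is no inflation beyond simulation noise.
- Stratified list, no centre term: the contrast varies with variance 25, but the test uses 25 + 2.67 = 27.67 or 25 + 10.67 = 35.67. The effective critical value rises from 2.39 to 2.39 × √(27.67/25) = 2.52 or 2.39 × √(35.67/25) = 2.86, so the level is about 1.2% or 0.4%. Simulation gave 1.0–1.4% and about 0.5%. The test is conservative.

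**4. Power for 3 points, 44 per arm, t test at two-sided 1.67%.**

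| Centre effects | SD in the test without the term | Power without the term | Power with centre in the model (simulated) |
|---|---|---|---|
| none | 5.00 | about 0.65 | about 0.01 lower at most |
| -2/0/+2 | √27.67 = 5.26 | about 0.59 | about 0.63 |
| -4/0/+4 | √35.67 = 5.97 | about 0.46–0.47 | about 0.63 |

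Leaving the term out costs about 0.04 at the lower assumption and about 0.17–0.18 at the upper. Putting it in costs at most about 0.01 if centres do not differ.

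**The case against.** **The list may already be stratified.** The text says where the table was generated, not that one unstratified list serves all three centres. Stratification and block details are often left to the full protocol, which is not shown. This stands. A reader might infer a plain, unblocked table, under which exactly 44/44/44 would arise in only about 0.6% of trials. The article does not state such a scheme, and its promise of equal groups points to some restriction.

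**Chance imbalance is not bias.** It averages zero, and the standard error allows for it. This also stands: type I error stays near nominal. A reader might infer that centre differences would be read as treatment effect, but ordinary sampling error alone already has a 95% bound of 1.96 × 5 × √(2/44) = 2.1 points. Adding the centre shift in quadrature gives √(2.1² + 0.7²) = 2.2 or √(2.1² + 1.4²) = 2.5.

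**The routes for a centre effect are narrower than they look.** The evaluator at each centre rates every visit, so a constant rater offset cancels in change scores. Only centre differences in recovery, or rater drift, remain. The same therapists treat all arms within a centre, so they matter only through centre imbalance. Routine care is not said to differ by centre, and two of the three sites are one hospital and its branch. All of this stands, and it makes the upper assumption look generous.

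**Covariates belong in the analysis plan.** This carries less weight. The article does not merely leave the model open: it names the between-subject factor, and that factor is treatment group alone.

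**Conclusion.** The point holds as one of precision and of uncorrected realised imbalance. Centre-specific evaluation and therapy are stated, the model's factors are stated, and centre is not among them. The documents do not support a claim of systematic bias, of inflated type I error, or that one unstratified list is in use.

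The size depends wholly on the assumed centre effects. At ±2 to ±4 points, the chance shift is bounded at about 0.7 to 1.4 points and the power loss for the 3-point contrast is about 0.04 to 0.18. If centres do not differ, there is no loss. The centre term is worth having whichever list is used: it recovers precision if the list is unstratified, and restores the nominal level if it is stratified.

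**What to change.** 1. Add centre as a fixed factor (2 degrees of freedom) to the FMA-UE and ARAT between-group comparisons. Because the outcome is change, centre should enter the repeated measures ANOVA together with its interaction with time; a main effect alone would leave the time-by-group test untouched. The cost is one model term and, if centres do not differ, about 0.01 of power at most.
2. State whether the allocation list is stratified by centre. If it is, nothing in the randomisation needs to change.
3. If it is not, have the independent statistician issue one envelope series per centre for patients still to be enrolled, in permuted blocks of varying size not disclosed to the sites. Patients already randomised (12 enrolled at submission, according to Trial status) keep their allocation. The cost is new lists and envelopes. The small downside is slightly more predictable allocation at sites where therapists and physicians are unblinded, limited by the varying block sizes.
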